### Study design

This proof of concept will take the form of a randomised controlled trial to be completed across three centres in Europe; the German Sport University Cologne, Germany, University of Nijmegen, The Netherlands and Trinity College Dublin, Ireland. A total of 225 participants will be randomised (*n* = 75 at each site) to either a yearlong supervised and home based aerobic exercise programme (*n* = 75), an equivalent non-aerobic stretching/toning programme (*n* = 75) or to the control group (*n* = 75). The primary outcome will be change in cognitive performance as measured by a neuropsychological test battery. Secondary outcomes will include changes in MoCA scores, cardiovascular fitness, physical activity, quality of life measures, measures of frailty, epigenetic and structural changes. Change in all outcomes will be measured at baseline (T0), after six months (T1) and after 12 months (T2) (see Fig. 1).

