### Randomisation, allocation, concealment and blinding

Following baseline assessment, participants will be randomised to one of three arms using a centrally controlled computer generated randomisation list (for each country) generated by an independent statistician. Participants will be randomised to one of three arms as per Fig. 1. At each centre, the investigators will be blinded to allocation order and the treatment will be assigned using sealed envelopes based on order of recruitment. Outcome assessors and exercise trainers will not be blinded to the allocated treatment arm.

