### Sample size

The sample size estimation was performed in “G*Power”, a statistical software program. The effect size was estimated, based on the effect size found in several studies examining the effect of exercise on cognition in elderly with MCI or increased risk for AD [8–10, 61, 62]. Sample size was calculated based on a two-tail statistical t-test set 1-β = 0.80, α = 0.05, an effect size of 0.4, an allocation ratio N2/N1 of 2. A total sample size of 224 was calculated. Considering a correlation of 0.5 between the outcome measures at T0 and T2, the design design-factor D = 1-0.52 = 0.75. The expected dropout rate is 25%. 224*0.75*1.25 = 210. Considering the fact that the primary analysis will be a combination of the results of three different centres, the final sample size *n* = 210 is rounded up to *n* = 225.

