### Statistical analysis

The primary analysis of this study will be comparison of cognitive functioning (primary outcome measure) between all three intervention arms before (T0) and after (T2) the 1 year intervention. A composite score will be calculated by averaging all six domain scores into one overall cognition score. The obtained scores per test will be converted into z-scores based on the standard deviation and mean of the total sample at baseline. In case of multiple tests within one domain, the average z-score for the domain will be calculated. Secondary outcome measures are the six separate cognitive domain scores and the other parameters.

For the primary analysis we will have an intervention group of *n* = 150 (both exercise forms together) and a control group of *n* = 75 as input of an ANCOVA with dependent variable the change in cognitive composite score between T2 and T0, and as covariates baseline cognitive functioning, sex, age. In a secondary analysis the comparison between the two exercise forms will be carried out in a similar ANCOVA analysis.

Analyses for all secondary outcome parameters will be carried out with similar ANCOVA analyses. Secondary analyses will also elucidate the contrasts between T0 and T1 and T2 for the primary and secondary outcomes, and thus elucidate the course over time, without correction for multiple comparisons, as these analyses are exploratory.

Furthermore, to assess change in physical fitness, quality of life, cerebral structure and epigenetics a similar statistical approach will be used as for the primary study parameter. A *p*-value of < 0.05 will be used to assess statistical significance.

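### Randomisation is stratified by country, but the primary ANCOVA omits site; if site predicts change, this costs some precision and does not raise the false-positive rate

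*Protocol article*

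**What the plan says.** Under Randomisation, allocation, concealment and blinding, allocation comes from a "centrally controlled computer generated randomisation list (for each country) generated by an independent statistician". Study design names three centres, one each in Germany, the Netherlands and Ireland, with 75 participants per centre. Country and site are therefore the same factor, and randomisation is stratified on it.

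Under Statistical analysis, the primary model is an ANCOVA on the T0 to T2 change in the composite, both exercise arms together against control, with "as covariates baseline cognitive functioning, sex, age". No section adds a site, centre or country term. For the aerobic against stretching comparison, "the comparison between the two exercise forms will be carried out in a similar ANCOVA analysis". For the rest, "Analyses for all secondary outcome parameters will be carried out with similar ANCOVA analyses". Neither sentence gives a covariate list of its own.

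The Sample size section does recognise the multicentre structure: "Considering the fact that the primary analysis will be a combination of the results of three different centres" is its reason for rounding 210 up to 225.

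**The concern.** An analysis should normally carry the factors used to stratify the randomisation. Leaving out a stratum that predicts the outcome keeps between-site variance in the error term. If the arms are balanced within site, the estimate itself does not vary with site, but its reported standard error behaves as though it did, so the test is conservative. If they are not balanced, chance imbalance between arms across sites adds real noise to the estimate. Dropout, expected at 25%, can create such imbalance even where allocation was balanced. Raising the sample size from 210 to 225 does not take site variance out of the error term.

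The article gives some reason to expect that site could matter. The z-scores use the mean and SD of the whole sample, so standardisation does not remove site differences. The word-list and fluency tests are verbal, and the sites are in three countries; different test languages are a fair inference but are not stated. The clearest case is a secondary outcome. Cardiovascular fitness is measured by a maximal test in Cologne and Dublin but estimated from a submaximal test in Nijmegen, so for that outcome site is partly also measurement method.

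At stake is efficiency in a trial planned for 80% power.

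**Working it through.** **Inputs from the Sample size section.** "two-tail statistical t-test set 1-β = 0.80, α = 0.05"; "an effect size of 0.4, an allocation ratio N2/N1 of 2"; T0 to T2 correlation 0.5; dropout 25%.

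**Input not in the document.** The share r of residual variance in change that site explains. I take 0%, 5%, 10% and 20% as an assumed range.

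**1. Reproduce the plan's figure.** The normal approximation gives 74 + 148 = 222. The noncentral t at 74 v 150 (total 224) gives power 0.8006, so the stated 224 reproduces. Then 224 × 0.75 = 168 and 168 × 1.25 = 210, as printed. Dividing by 0.75 for dropout instead would give 224, still below 225.

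**2. Reference case.** Take the 168 planned completers as 56 control v 112 exercise, with residual variance 1 − 0.5² = 0.75.
- SE = sqrt(0.75 × (1/56 + 1/112)) = 0.1417.
- Noncentrality = 0.4/0.1417 = 2.82.
- Power = 80.1%.

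**3. Arms balanced within site.** The true sampling variance uses 0.75(1 − r), but the model without site reports 0.75. Its SE is therefore too large by f = 1/sqrt(1 − r).
- Actual alpha without site = 2 × P(T > f × t_crit).
- Power without site: noncentrality 0.4/sqrt(0.75(1 − r)(1/56 + 1/112)) against critical value f × t_crit.
- Power with site: the same noncentrality against t_crit, with 2 fewer degrees of freedom.

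| r (assumed) | SE factor f | Actual alpha, no site | Power, no site | Power, with site | Gain (from unrounded values) |
|---|---|---|---|---|---|
| 0% | 1.000 | 0.050 | 80.1% | 80.1% | 0 |
| 5% | 1.026 | 0.044 | 80.7% | 82.1% | 1.4 points |
| 10% | 1.054 | 0.039 | 81.3% | 84.1% | 2.7 points |
| 20% | 1.118 | 0.029 | 82.7% | 88.0% | 5.3 points |

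**4. Lists not blocked.** Site variance then really does enter the sampling variance of the estimate. The SE without site is valid and alpha stays at 0.05. Power is 80.1% without site against 82.1%, 84.1% and 88.0% with it, a gain of about 2, 4 and 8 points.

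**5. Simulation check** (6,000 trials per setting, 168 completers, three sites).
- Balanced, r = 20%: without site the mean reported SE is 0.1415 against an empirical SD of 0.128; with site it is 0.126 against 0.128.
- Unblocked, r = 20%: without site 0.143 against 0.143; with site 0.128 against 0.129. Simulated power is 79.3% without site and 86.9% with it, slightly below the formula because uneven arms within sites cost a little.
- Unblocked, r = 0: power is 80.2% without site and 79.7% with it, a difference of the order of simulation error.

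**The case against.** The strongest reply is that this is a small efficiency point whose size the document cannot establish. Much of that stands.

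- **The consequence is conditional.** A reader might infer that the standard errors are simply too large. That needs site to predict adjusted change and the arms to be balanced within site. The article gives no figure for the first and does not state blocking.
- **The gain is easy to overstate.** A reader might set 82%, 84% and 88% against a fixed 80% in every case. That comparison fits unblocked lists only. With balance within site, power without the site term also rises, and the gain falls to 1.4, 2.7 and 5.3 points.
- **The upper end of the range is hard to reach.** Baseline adjustment removes part of any stable site difference. At a T0 to T2 correlation of 0.5, stable differences would have to explain about 13–16% of composite variance to leave r = 5%, 23–33% for 10%, and 38–75% for 20%. The ranges depend on whether 0.5 is read as the overall or the within-site correlation. Site differences in the rate of change could add to r, but the article reports none.
- **Some apparent site differences carry little weight.** The entry memory test differs by site, but it applies to community recruits and is not an outcome. Nothing says that class delivery differs by site. The word-list and fluency tests might be taken to fill two of the six domains, but executive function also contains TMT-B. Their weight in the composite is (1 + 2/3)/6, about 28%.
- **The secondary models are less clear.** Their omission of site is read from the word 'similar'.

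The reply does not remove the point for the primary model. There the article names its covariates, and the list leaves out the stratification factor. That is a stated choice, not a detail left to another document.

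**Conclusion.** The point holds as an improvement in efficiency. The primary ANCOVA omits the factor on which randomisation was stratified, and the other ANCOVAs do so by inference. The loss depends on an unknown site share of residual variance. Over an assumed 5% to 20% it is about 1.4 to 5.3 points of power if arms are balanced within site, with a conservative test, and about 2 to 8 points if the lists are not blocked, with a valid but wider standard error. If the share is zero, essentially nothing is lost either way.

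A reader might infer a threat to validity. The documents do not support that: type I error is not inflated, no systematic bias in the treatment effect is shown, and the estimate remains interpretable. The omission itself is certain for the primary model; its practical size is not. The case for a site term is strongest for cardiovascular fitness, where the test itself differs by site.

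**What to change.** Add site (country) as a three-level fixed factor to the primary ANCOVA, alongside baseline cognition, sex and age. State that the similar ANCOVAs, including the comparison of the two exercise forms, carry the same term, with two levels for MRI outcomes because only Cologne and Nijmegen scan. Say also whether the country lists are blocked.

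The cost is 2 degrees of freedom in the three-site models. No further data or participants are needed, and the sample size need not change. Make the change before outcome data are analysed, since a site term added later could look data-driven.

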### Outcome assessment

All outcomes will be measured at T0 (Baseline), T1 (6 months) and T2 (12 months) time points. Brain MRI, blood sampling for epigenetic analysis and the NEO-Five Factor Inventory (NEO-FFI) will only be measured at T0 and T2. All participants will undergo described tests, except for MRI (only in Cologne and Nijmegen).

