Venous blood samples will be collected for genetic and epigenetics analysis performed on a Sequenom Massarray Analyzer 4 at the Department of Psychology University of Bonn, Germany. Genotyping of the Apolipoprotein E (APOE) and the Brain Derived Neurotrophic Factor (BDNF) genes and their epigenetic methylation patterns will be the primary focus. The genetic analyses will serve as predisposed risk and resilience factors for cognitive functioning and decline in MCI participants. The epigenetic findings will shed new light on the link between exercise and gene activation of relevant genes in the biochemical pathways underlying cognitive decline. Given the moderating effect of the common genetic variation of APOE via personality on AD onset [58], the NEO-Five Factor Inventory (NEO-FFI) will be included to assess personality traits such as neuroticism or extraversion, predicting an earlier onset of Alzheimer and cognitive decline in elderly humans [59]. NEO-FFI is a psychological personality inventory consisting of 60 items to measure five personality traits. The questionnaire will be completed following each blood draw to form part of the epigenetics analysis. The NEO-FFI is also discussed as a measure of emotional intelligence [60].

Structure and function of related brain regions will be measured using functional MRI (fMRI) brain which is a non-invasive method for examining brain activity and structure. Structural imaging will include isotropic T1-weighted-, T2-weighted- and FLAIR- sequences with an isotropic spatial resolution of 1x1x1mm. The combination of the different image weightings allows for an automatic detection/volumetry of white matter lesions. Additionally, the combination of these sequences improves image segmentation. The structural protocol will be rounded up by a 3D-DTI sequence (60 diffusion directions, 1.7x1.7x1.7 mm) and a resting state fMRI Table 1.

**Table 1 Tab1:** SPIRIT diagram outlining schedule of enrolment, interventions, and assessments for study participants

Timepoints		Pre-screening telephone call	Baseline assessment T0	Study assessment T1	Study assessment T2
			<13 days following screening	6 months after study visit 1	12 months after study visit 1
Enrolment	Explain study	X			
	Screen eligibility criteria	X			
Study Outcomes	Neuropsychological testing		X	X	X
	MoCA		X	X	X
	DemQOL		X	X	X
	CES-D		X	X	X
	Incremental Exercise Test		X	X	X
	Physical Activity Tracker		X	X	X
	LAPAQ		X	X	X
	Blood sampling		X		X
	NEO-FFI		X		X

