## Discussion

To the best of our knowledge, there have been no intervention trials evaluating the effect of an extensive, controlled and structured 12-month exercise programme on the progression of cognitive decline in an MCI population. Since the neuropathological change process can take years after onset of MCI, the addition of longer intervention period may result in larger intervention effects. An important consideration of this study is the isolated aerobic exercise intervention. A number of exercise intervention studies have implemented multimodal exercise interventions [11, 63], making it difficult to interpret the effect of isolated exercise modalities. The large sample size, longer duration of exercise intervention, comprehensive neuropsychological test battery will enhance the existing research around exercise and cognitive function in MCI.

The secondary outcomes will examine several potential underlying mechanisms that may influence the exercise-cognitive relationship in MCI. The effect of exercise on brain structure and function measured by MRI brain will be examined. Methylation analyses of the APOE gene and neurotrophic genes will explore the effects of exercise on this known AD risk factor. Static gene polymorphisms will be used to predict intervention outcomes. Finally, cardiovascular fitness will be measured and examined as a moderator of the exercise-cognitive relationship in MCI. While cognitive performance is the primary outcome, we will also assess whether participation in a structured exercise programme or changes in cognition can influence quality of life and measures of frailty, known risk factors for cognitive further decline [64].

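### The primary ANCOVA is valid as written, but could gain a little precision by prespecifying baseline APOE genotype, which the protocol already collects and treats as prognostic

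*Protocol article*

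**What the plan says.** Protocol article, Statistical analysis: the primary comparison sets "an intervention group of *n* = 150 (both exercise forms together) and a control group of *n* = 75" against each other in an ANCOVA of the change in composite score from T0 to T2, with "as covariates baseline cognitive functioning, sex, age". Secondary outcomes are to be analysed with similar models.

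Protocol article, Secondary outcomes: the main focus of the blood work is "Genotyping of the Apolipoprotein E (APOE) and the Brain Derived Neurotrophic Factor (BDNF) genes", together with their methylation patterns. The purpose of the genetic part is stated: "The genetic analyses will serve as predisposed risk and resilience factors for cognitive functioning and decline in MCI participants".

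Protocol article, Outcome assessment: "blood sampling for epigenetic analysis and the NEO-Five Factor Inventory (NEO-FFI) will only be measured at T0 and T2". On who is tested: "All participants will undergo described tests, except for MRI", which is done at two of the three sites. Table 1 places randomisation after all baseline assessments.

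Protocol article, Discussion: APOE is referred to as an established risk factor for AD, and "Static gene polymorphisms will be used to predict intervention outcomes".

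**The concern.** The protocol regards the genetic data as prognostic for the very thing the primary outcome measures, cognitive decline over the year. It collects the material from everyone before randomisation and plans to relate genotype to outcome. The confirmatory model nevertheless makes no use of it.

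A covariate that predicts change beyond those already in the model reduces residual variance and narrows the confidence interval for the exercise effect. The design has little power to spare: on the protocol's own assumptions it sits almost exactly at 80% once the expected dropout has occurred. What is at stake is therefore a small amount of precision in the primary comparison. Its validity is not in question.

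**Working it through.** **Inputs from the protocol article (Sample size; Statistical analysis).** Two-sided α = 0.05, power 0.80, d = 0.4, allocation 2:1, T0–T2 correlation 0.5, dropout 25%, 225 randomised as 150 and 75.

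**Input not in the documents.** The share of residual variance that APOE explains beyond baseline score, sex and age (partial R²). Assumed range 0 to 0.05, with 0.10 as an extreme.

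**1. The plan's own figure.** Power for two means comes from the noncentral t distribution with noncentrality d × √(n1·n2/(n1+n2)). With 149 and 75 (total 224) and d = 0.4, the noncentrality is 2.825 on 222 degrees of freedom and power is 0.803. The stated 224 reproduces. The design factor is 1 − 0.5² = 0.75, so 224 × 0.75 = 168 evaluable participants are needed.

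**2. Power of the model as written.** After 25% dropout, 225 × 0.75 = 168.75 remain, that is 112.5 and 56.25. The effect in residual SD units is 0.4/√0.75 = 0.462. The noncentrality is 0.462 × √(112.5 × 56.25/168.75) = 0.462 × 6.124 = 2.828, and power is 0.803.

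**3. Power with APOE added.** Residual variance becomes 0.75 × (1 − R²), so the effect becomes 0.4/√(0.75 × (1 − R²)). The standard error is multiplied by √(1 − R²). The equivalent number of additional randomised participants is 225 × (1/(1 − R²) − 1).

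| Assumed partial R² | Power | SE multiplied by | Equivalent extra randomised |
|---|---|---|---|
| 0 | 0.803 | 1.000 | 0 |
| 0.01 | 0.807 | 0.995 | 2.3 |
| 0.03 | 0.815 | 0.985 | 7.0 |
| 0.05 | 0.823 | 0.975 | 11.8 |
| 0.10 (extreme) | 0.842 | 0.949 | 25 |

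These figures charge no degrees of freedom for covariates. Charging three for the existing covariates and one or two more for APOE lowers power by no more than about 0.0002 in any row. At R² = 0, adding APOE therefore costs practically nothing.

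**4. What such an R² would mean.** For carrier share p and a carrier difference of b residual SD, R² = v/(1 + v) with v = p(1 − p)b². With p = 0.4 (assumed), b = 0.2, 0.3 and 0.5 give R² of about 0.01, 0.02 and 0.06.

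**5. Chance imbalance in carriers.** With an assumed carrier share of 45%, the SD of the difference in carrier proportion between groups is √(0.45 × 0.55 × (1/112.5 + 1/56.25)) = 0.081. With a carrier difference of 0.2 to 0.3 residual SD (assumed), a one-SD imbalance moves the estimate by 0.081 × 0.2 = 0.016 to 0.081 × 0.3 = 0.024 residual SD. The standard error of the treatment difference is √(1/112.5 + 1/56.25) = 0.163 residual SD, so the shift is about 10 to 15% of one standard error.

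**The case against.** The strongest case against raising this is that nothing is wrong. The covariate list is prespecified, and under randomisation an omitted prognostic factor neither biases the estimate nor inflates type I error. The sample size takes credit only for the T0–T2 correlation, so there is no inconsistency. All of that stands.

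The gain also rests on a partial R² that the documents do not give. It falls to nil if baseline score, sex and age already carry the APOE signal. That stands too, and is why the range starts at zero.

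Three stronger readings are tempting, and the documents do not support them:

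- A reader might infer that the 0.5 correlation, which leaves 75% of T2 variance unexplained, shows that baseline cognition does not absorb the APOE effect. It does not. The unexplained part may come from other sources, including measurement error, and says nothing about APOE's share.
- A reader might infer that a chance imbalance in carriers distorts the primary result. Any imbalance is first scaled by the carrier effect, and this variation is already reflected in the standard error.
- A reader might call the gain free. It makes the primary analysis wait for a separate laboratory workstream and needs a rule for missing genotypes.

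Two further objections carry less weight. The article describes depression, personality, quality of life and frailty in similar prognostic terms, so APOE is not the only candidate, and a short covariate list is a legitimate choice. Genotype also already has a secondary role as a predictor of outcome. Neither makes adding this one fixed baseline covariate harmful.

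**Conclusion.** The point holds as an optional improvement in precision. APOE genotype meets the conditions for a good covariate: it is sampled at T0 before randomisation, planned for all participants, unaffected by treatment, and regarded as prognostic by the protocol itself. It is absent from the primary model.

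The benefit is small: between 0 and 2 percentage points of power (80.3% to at most 82.3%) for an assumed partial R² of 0 to 5%, at d = 0.4 and about 169 evaluable participants. That is worth at most about 12 randomised participants. It rests on the assumed R², on the protocol's own effect size, correlation and dropout, and on near-complete genotyping. The primary test is valid without it, and the judgement that the trial has about 80% power does not change.

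**What to change.** Prespecify APOE e4 carrier status as an added covariate in the primary ANCOVA and in the similar ANCOVAs for the cognitive outcomes. Code it yes or no, with a third level for participants not genotyped, so that nobody with an outcome is dropped and the intention-to-treat set is preserved. State this before outcome data are examined, so that adjustment cannot look like a response to an observed imbalance.

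The cost is a change of wording in the analysis plan, one or two degrees of freedom out of roughly 160, and the requirement that genotyping be complete before the primary analysis is run. If the laboratory timetable cannot guarantee that, keeping the present covariate list is defensible.

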### Recruitment and screening

In total, 225 previously sedentary adults aged 50 years or older who are diagnosed with MCI will be recruited via hospital memory clinics affiliated with the three sites and from the community. Advertising will take place through community centres and newspaper articles. Initial screening will be completed over the telephone to determine eligibility. Participants who meet the following diagnostic, inclusion and exclusion criteria and successfully complete baseline measures including a screening exercise test will be enrolled.

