### Inclusion criteria

Participants who meet the following criteria will be eligible to participate: (1) MoCA [31] 18–26; (2) stable medical condition for more than 6 months; (3) stable medication for more than 3 months; (4) adequate visual and auditory acuity to complete neuropsychological testing; (5) electrocardiogram without significant abnormalities that might interfere with the study; (6) physical ability sufficient to allow performance of endurance exercise training; (7) capacity to provide written and dated informed consent form; (8) medical clearance to undergo a symptom-limited cardiopulmonary exercise test and extensive aerobic exercise training.

Participants recruited from the community via newspaper articles and community advertisement will complete additional testing to determine MCI status. To distinguish between amnestic and non-amnestic MCI, agreed education adjusted cut-offs of -2 Standard Deviation (SD) for low education (<10 years of education), -1.5 SD for the middle group (10–13 years of education) and -1 SD for the highly educated (>13 years of education) will be taken from the delayed recall portion of an age adjusted episodic memory test. In Nijmegen and Dublin this will be evaluated using the Logical Memory (story recall) subtest of the Wechsler Memory Scale (WMS-IV) [32, 33]. In Cologne, education scores will be examined using the Repeatable Battery for the Assessment of Neuropsychological Status (RBANS) [34] Delayed Memory Index (Score of < 85).

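### The primary ANCOVA adjusts for baseline cognition, sex and age but not years of education; adding education would be a small, optional gain in precision

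*Protocol article*

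**What the plan says.** All references are to the protocol article.

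- **Statistical analysis, model.** The primary ANCOVA compares 150 exercisers ("both exercise forms together) and a control group of" 75). The dependent variable is "the change in cognitive composite score between T2 and T0", and the covariates are "baseline cognitive functioning, sex, age". The secondary outcomes, including the six domain scores, are to be analysed in similar ANCOVAs.
- **Statistical analysis, scaling.** Test scores are "converted into z-scores based on the standard deviation and mean of the total sample at baseline", then averaged within domains and across the six domains. No education norming is stated.
- **Inclusion criteria.** Community recruits have extra testing. The delayed-recall cut-off, on an age-adjusted memory test, is -2 SD below 10 years of education and -1 SD above 13 years. The middle step, after its minus sign, reads "1.5 SD for the middle group (10–13 years of education". For Cologne the section names an RBANS Delayed Memory Index below 85.
- **Sample size.** "Considering a correlation of 0.5 between the outcome measures at T0 and T2", the plan uses a design factor of 0.75.
- **Randomisation.** There is one list per country. No stratification by education is stated.

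**The concern.** The plan treats education as relevant to memory scores when it classifies community recruits: the cut-off moves by a full SD between the lowest and highest bands. The same rule uses an age-adjusted test, and age is carried into the primary model while education is not. Because the composite is scaled only to the trial's own baseline mean and SD, any education-related differences between participants stay in it.

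Baseline cognition will absorb part of this. Whether it absorbs all of it depends on how closely T0 predicts T2. At the assumed correlation of 0.5, three quarters of the T2 variance is unexplained by baseline, so a stable characteristic related to cognition could still carry information.

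At stake is residual variance in the primary comparison, and adjustment for a chance imbalance in education between a control arm of 75 and 150 exercisers. Planned power is only just above 80%, so cheap precision is of some use.

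**Working it through.** **1. Inputs from the Sample size section.** Two-sided α = 0.05, power 0.80, effect size 0.4, allocation 2:1, T0-T2 correlation ρ = 0.5, dropout 25%, planned N = 225.

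**2. The plan's own figures.** The noncentral t with 75 and 149 participants gives power 0.803. With 74 and 149 it gives 0.7997. The stated 224 therefore reproduces. The design factor is 1 - 0.5² = 0.75, and 224 × 0.75 = 168; 168 × 1.25 = 210. Both follow as stated.

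**3. Starting power with the listed model.** With 25% loss, 225 × 0.75 = 168.75 are analysed, split 56.25 and 112.5. The standardised effect is 0.4/√0.75 = 0.462, and the noncentral t gives power 80.3%. As in the plan, only the baseline correlation is credited; age and sex are not. Analysing change with baseline as a covariate gives the same treatment effect and residual variance as analysing T2 with baseline as a covariate, so the factor 0.75 applies.

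**4. What education could add.** Let a and b be the correlations of education with the composite at T0 and T2. The partial correlation of education with T2 given T0 is

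(b - ρa) / √[(1 - ρ²)(1 - a²)].

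Its square, p, is the share of residual variance removed. The documents give neither a nor b, so the values below are assumptions.

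Equal correlations (a = b), ρ = 0.5:

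| a = b | Partial correlation | p | Residual variance 0.75(1 - p) | Equivalent extra participants, 168.75 × [1/(1 - p) - 1] | Power |
|---|---|---|---|---|---|
| 0.2 | 0.118 | 1.4% | 0.740 | 2.4 | 80.8% |
| 0.3 | 0.182 | 3.3% | 0.725 | 5.8 | 81.6% |
| 0.4 | 0.252 | 6.3% | 0.702 | 11.4 | 82.8% |

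Worked case: a = b = 0.3 gives (0.3 - 0.15)/√(0.75 × 0.91) = 0.15/0.826 = 0.182.

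**5. Sensitivity to the two assumptions.**

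- *Weaker link with T2.* If b = a/2, the numerator is a/2 - 0.5a = 0. So p = 0 and nothing is gained.
- *Stronger T0-T2 correlation.* At ρ = 0.7 with a = b, p is 0.7% at 0.2 (partial correlation 0.086) and 3.4% at 0.4 (0.183).

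**6. Chance imbalance.** The standard error of a difference in mean education between arms is √(1/56.25 + 1/112.5) = 0.163 SD. With a = b, the coefficient of education given T0 is 0.5a/(1 - a²) = 0.104, 0.165 or 0.238. For an imbalance of one standard error at equal baseline scores, the shift is 0.163 times the coefficient: 0.017, 0.027 or 0.039 SD, against a target effect of 0.4.

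**The case against.** The strongest objection is that this is a preference and not a fault. In a randomised comparison, an ANCOVA on baseline, age and sex is valid. Leaving out another prognostic variable neither biases the effect nor inflates type I error. The sample size credits only the T0-T2 correlation, so no stated figure depends on education, and no stratification by education is stated that would call for it in the model. All of this stands.

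Four stronger readings are tempting, and the documents do not support them:

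- *That a correlation of 0.5 makes education predictive.* It leaves 75% of the T2 variance unexplained by baseline, but does not say what explains it. That needs a partial correlation which the article does not give and which can be zero.
- *That education sets entry to the trial.* The bands apply to community recruits only, to separate amnestic from non-amnestic MCI. The criteria for everyone (MoCA 18-26, Clinical Dementia Rating 0.5) carry no education adjustment.
- *That recruitment source should be added too.* Participants come from "hospital memory clinics affiliated with the three sites and from the community", but nothing gives the proportions or says that prognosis differs by route, so no gain can be estimated.
- *That precision is certainly being lost.* The range starts at nil. Age and sex, already in the model, could also absorb part of any education effect, which the figures above ignore.

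It is also fair to say that the plan already meets its 80% target and that the plausible imbalance effect is small. What survives is that the covariate list is fixed in the text, education is a variable the plan itself uses when judging memory scores, and adding it costs almost nothing.

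**Conclusion.** The point holds as an optional improvement of low priority, not as an error. Under equal correlations of 0.2 to 0.4 with T0 and T2 and the plan's ρ = 0.5, adjustment for education removes about 1% to 6% of residual variance. Power rises from 80.3% to between 80.8% and 82.8%, a gain of roughly 0.5 to 2.5 points, worth about 2 to 11 of some 169 analysed participants. The gain falls to nil if education's correlation with T2 is half that with T0, and shrinks if ρ exceeds 0.5. The education correlations are assumptions, so the size is illustrative.

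**What to change.** Before any analysis of outcomes by arm, pre-specify years of education, entered linearly, as an additional covariate in the primary ANCOVA and in the ANCOVAs for the cognitive secondary outcomes. Record it at baseline for all participants. Pre-specification matters because a covariate added after results are seen would be open to challenge.

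The cost is one line of analysis wording, one degree of freedom, and one baseline question for clinic recruits; community recruits already need it for the memory cut-offs. The sample size needs no change.
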